## Abstract

**Background:**

Both **s**evere stenosis and completed occlusion in internal carotid artery or its distal branches have been considered the main reasons of cerebral hypoperfusion, which contributes to the washout disturbances of embolism in low perfusion territories distal to stenosis. An aggravated hypoperfusion state in certain brain region may induce ischemic stroke and further cognitive decline. However, the effective medication for cerebral hypoperfusion is largely unsettled.

**Methods/design:**

By using computed tomography perfusion (CTP) imaging, the trial will evaluate the effectiveness, safety and tolerability of hydroxyethyl starch (HES) 130/0.4 for patients with extra-/intra-cranial artery stenosis and cerebral hypoperfusion. From 5 neurological inpatient wards, 300 patients will be randomly recruited for administered routine medications plus intravascular volume therapies using the equal volume of HES 130/0.4 or 0.9% sodium chloride solution. Cerebral hypoperfusion state after 7-day intervention is the primary outcome measure. The secondary outcome measures includes, impaired renal function, abnormal heart function, hematological changes, neurological dysfunctions and cerebrovascular events in peri-intervention period and/or 3-month follow-up. The sample size will allow the detection of a two-sided 5% significance level between groups in the endpoint with a power of 80%.

**Discussion:**

The trial would provide important efficacy and safety data on the intravascular administration of HES 130/0.4 in patients with unilateral cerebral hypoperfusion. The effects on kidney function, heart function, coagulation, neurological function and cerebralvascular events will be assessed.

**Trial registration:**

ClinicalTrials.gov (Identifier: NCT01192581)

## Background

### Large-artery stenosis-induced cerebral hypoperfusion

As a subtype of the TOAST or CISS classification for ischemic stroke [1,2], large-artery atherosclerosis commonly induces internal carotid artery (ICA) or its distal branches (middle cerebral artery, MCA) stenosis. Severe artery stenosis is the major prognostic stroke risk factor in patients with symptomatic and asymptomatic ICA/MCA disease, and would place hemodynamic stress on the brain circulation. Among asymptomatic patients, increasing frequencies of transient ischemic attack (TIA) and stroke is related to grades of arterial stenosis. In patients with symptoms including transient monocular blindness, TIA and minor strokes, stroke risk highly related with the severity of ICA/MCA stenosis [3,4].

Cerebral hypoperfusion is deemed as an important origin contributed to ischemic stroke or reversible neurological dysfunctions in patients with extra-/intra-cranial arterial stenotic or occlusive disease [5]. Large-artery-stenosis induced cerebral hypoperfusion leads to blockage in smaller distal artery, which would decrease perfusion in the local region. In some cases, embolic materials from proximal artery might appear washout disturbances to increase the degree of artery stenosis. A prolonged failure to deliver oxygen and sugar-rich blood to brain tissue causes a metabolic impairment of neural cells, in severe conditions, irreversible cells death, i.e. cerebral infarction.

### Management of cerebral hypoperfusion

Treatments of ICA/MCA stenosis and secondary stroke-prevention related to intracranial arteries atherosclerosis have been extensively explored under numbers of investigations [6]. However, enough importance has not been attached to the management of cerebral hypoperfusion yet. It is well known that tPA is almost the only effective treatment for patients with acute ischemic stroke, which improves the perfusion state of ischemic penumbra by dissolving the blood clot. Because of the narrow therapeutic window, the use of tPA is largely restricted. Apart from this, antiplatelet therapy, statins therapy and risk factor modifications, as routine medications, are recommended for patients with large-artery atherosclerosis. In invasive treatments, carotid endarterectomy (CEA) is recommended for symptomatic patients with moderate to high grade stenosis (50%–99%). Carotid angioplasty and stenting (CAS) has been indicated as a therapeutic alternative to CEA [7,8], which exerts improving perfusion state in cerebral hypoperfusion region [3,9]. However, the role of CAS remains uncertain and controversial for the asymptomatic patients with ICA stenosis. Recently, researchers reported an anti-migraine agent, lomerizine, could contribute to restoration of cerebral hypoperfusion by SPECT [10].

Theoretically, volume therapy attempts to improve cerebral perfusion of ischemic regions through optimization of hemorheological parameters and increment in cardiac output and blood pressure [11,12]. A previous study [13] confirmed the safety of hypervolemic therapy; however, the sample size was too small to show the clinical efficacy statistically. Furthermore, unfavorable results of volume therapy in acute ischemic stroke was reported by a meta-analysis [14] on survival or neurological function evaluation in 18 clinical trials. During recent decades, colloidal solutions are extensively used in the volume therapy of ischemic stroke in many countries [15]. However, the effect of medication on non-acute cerebral hypoperfusion state is still largely unsettled.

### The clinical effects of hydroxyethyl starches

Hydroxyethyl Starches (HES) is one of the worldwide-used colloidal solutions for decreasing hematocrit and whole-blood viscosity without significant effects on plasma viscosity and red-cell aggregation [16]. HES is classified according to the molecular weight (MW) into high MW (450±480 kDa), medium MW (130–200 kDa), and low MW (40–70 kDa) starch preparations, which exert different therapeutic and adverse effects respectively.

In comparison with other starch preparations, HES 130/0.4 marked for the indication ‘intravascular volume expansion and hemodilution’ in worldwide (Summary of Product Characteristics for Voluven, Fresenius Kabi) and showed advantages in the brain, such as an improvement of hemorheologic parameters, an earlier increase of tissue oxygen tension and a safety in large-dose infusion [17,18]. Mammalian study [19] further indicated that HES 130/0.4 played an anti-inflammatory role in non-brain tissues. However, the effect of HES 130/0.4 on cerebral hypoperfusion state is still unclear.

### Objectives of the study

The objectives of this study are to evaluate the effectiveness, safety and tolerability of consistent dosages of HES 130/0.4 administrated intravenously for 7 days in patients with cerebral hypoperfusion in unilateral ICA or MCA territory. We expect that the results will indicate the effect of HES 130/0.4 on cerebral hypoperfusion.

## Methods/design

### Participants

Total 300 inpatients will be recruited through 5 neurology wards of general hospitals in Xi’an, China. Three subtypes of patients will be enrolled: I, non-acute ischemic stroke (time of stroke onset: 72 hours to 3 weeks); II, TIA with cerebral hypoperfusion; III, asymptomatic cerebral hypoperfusion. Outpatients showed abnormal results in carotid color Doppler and transcranial Doppler (temporal bone window) in routine physical examination, would be enrolled as asymptomatic candidates for further evaluation of cerebral perfusion state.

Prior to data collection, ethics approval have been achieved through the Medical Ethical Reviewing Committee of the Fourth Military Medical University Medical Center. Informed consent will be supported by a patient (or next to kin) information leaflet in Chinese. A consulted meeting will be developed by a study physician to ensure patients and their families understand the study procedure and consent to participation in the trial [20].

### Study design

Multicenter, randomized, paralleled, double-blinded trial with concealed allocation of patients with cerebral hypoperfusion 1:1 to volume therapy using 6% HES 130/0.4 in 0.9% sodium chloride (Voluven, Fresenius Kabi, Germany) or 0.9% sodium chloride solution (normal saline, NS), is stratified by presence of stroke or not. We use digital subtraction angiography (DSA) to verify the severity of ICA or MCA stenosis [21], and evaluate cerebral hypoperfusion in unilateral intracranial artery territories by time to peak (TTP), one of parameters in CTP imaging [22].

### Sample size estimates

The results from our preliminary study were used to calculate the sample size (unpublished data). The mean difference and standard deviation of TTP after HES 130/0.4 were 19.83 and 10.21, respectively. A two-sided 5% significance level and 80% power were considered, and the following equation was used: 

$$n=\frac{2\times {\left(\zeta_{\alpha /2}+\zeta_{\beta }\right)}^{2}\times \sigma^{2}}{\delta^{2}}$$

Approximately 60 participants in each group were calculated to be required. A 20% attrition rate is anticipated over the 2-year study period, resulting in about 300 participants in total four groups as a final estimated sample size.

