**Figure 1 F1:**
[figure not shown]
Flowchart outlining the trial protocol.

Participants will be randomized to one of two interventions: HES 130/0.4 and NS with two daily dosages in each intervention, i.e. 500 ml and 1000 ml, for 7 consecutive intervention days. A range of outcome measures (Table 1) will be used to ensure evaluation of relevant variables, based on the primary and secondary aims of the trial, clinical relevance and feasibility. Patients will be enrolled initially in the 500 ml groups. If more than 30% patients experience intolerable adverse events, the trial should be stopped. Following successful completion of 500 ml dose study, patients should be enrolled in the 1000 ml groups.

According to our preliminary study, 60% (15/25) of patients were found infarct responsible focuses in MCA territory by MRI brain scanning. To ensure comparable groups in terms of neurological status, group assignment will be stratified by having infarct responsible focuses or not. An individual not associated with the trial will use a computerized random number generator to randomly assign subjects to group. Allocation concealment will be ensured by using opaque, a sealed envelope containing group assignment.

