### Intervention

All participants will receive routine medications including antiplatelet therapy, statins therapy, risk factor modification and others if necessary. Intervention group will receive a prescribed dose of 0.6% HES 130/0.4 in 7 intervention days. Control group will be treated the same volume of NS each day in the intervention period. The initial 10–20 ml will be infused slowly, keeping the patient under close observation.

Although, the infusion dose of HES 130/0.4 up to 33 mL/kg/day is most commonly used in clinical trials and repetitive large doses of up to 70 ml/kg/day have been reported in the literatures [23-26]. Considering potential risks of overloading the circulatory system and increasing brain edema by overdose and the median cumulative HES dose (2465 ml, range 328 ml to 6229 ml) in resuscitation [27], two dose groups (500 ml/day and 1000 ml/day) have been chosen as cumulative dose of 3500 ml and 7000 ml.

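### The 80% between-group power rests on a TTP difference described only as following HES; no HES-minus-saline difference is stated

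*Protocol article*

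**What the plan says.** Under Sample size estimates, the protocol article gives the source of its inputs, "The results from our preliminary study were used to calculate the sample size (unpublished data"), and then the inputs: "The mean difference and standard deviation of TTP after HES 130/0.4 were 19.83 and 10.21, respectively". It continues "A two-sided 5% significance level and 80% power were considered, and the following equation was used" and shows the formula for two independent means, n = 2(z_α/2 + z_β)²σ²/δ². The result is about 60 per group, raised for 20% attrition to about 300 in four groups.

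The Abstract (Methods/design) presents the result as between-group power: "The sample size will allow the detection of a two-sided 5% significance level between groups in the endpoint with a power of 80" per cent. Study design and Discussion make HES versus normal saline (NS) the comparison. Under Intervention the comparator is an active infusion: "Control group will be treated the same volume of NS each day in the intervention period".

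The only other description of the preliminary work is under Study procedures: "According to our preliminary study, 60% (15/25) of patients were found infarct responsible focuses in MCA territory by MRI brain scanning". That sentence does not say how the 25 patients were treated. I assume it refers to the same preliminary study.

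**The concern.** In the two-group formula, δ has to be the difference expected between the arms, here HES minus NS. The figure supplied is tied to HES alone. If it is a change from before to after HES, it contains everything that would also have happened under saline, and the between-arm contrast removes that part.

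The article gives two reasons why saline patients might change.

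- **Volume effect.** The control arm receives the same daily volume, and the Background says that in theory "volume therapy attempts to improve cerebral perfusion of ischemic regions". The Abstract describes both arms as volume therapy.
- **Selection.** Inclusion criterion 3 admits patients whose TTP is prolonged by at least 15% against the other side, so some regression to the mean is possible in both arms.

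At stake is how a null result would be read. It would be reported as coming from a trial with 80% power, when the power for the HES-versus-saline contrast has not been established.

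**Working it through.** **Inputs.** From Sample size estimates: mean difference 19.83, SD 10.21, two-sided α = 0.05, power 0.80, about 60 per group, 20% attrition. (z_α/2 + z_β)² = (1.960 + 0.842)² = 7.849. The units of TTP are not given. The saline change is not given either, so it is varied below as an assumed share of the HES change.

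**1. Reproduce the stated 60.**
- As printed (δ = 19.83, σ = 10.21): n = 2 × 7.849 × 10.21² / 19.83² = 2 × 7.849 × 104.24 / 393.23 = 4.16, so 5 per group. Neither a one-sided test (4), nor 99% power (10), nor the paired form (2.1) comes near 60.
- Exchanged (δ = 10.21, σ = 19.83): n = 2 × 7.849 × 393.23 / 104.24 = 59.2, so 60 per group, which matches.
- Attrition: 60 / 0.8 = 75 per group, and 75 × 4 = 300, which matches.

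The stated size therefore follows only if the two values are exchanged.

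**2. Power at 60 per group when saline also changes.** Net difference = HES change × (1 − f), where f is the saline share (assumed). Two-sample t-test, two-sided 5%.

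| f | Exchanged: net difference (SD 19.83) | Power | As printed: net difference (SD 10.21) | Power |
|---|---|---|---|---|
| 0 | 10.21 | 80% | 19.83 | >99.9% |
| 10% | 9.19 | 71% | 17.85 | >99.9% |
| 20% | 8.17 | 61% | 15.86 | >99.9% |
| 33% | 6.81 | 46% | 13.22 | >99.9% |
| 50% | 5.11 | 29% | 9.92 | >99.9% |

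**3. Margin on the printed values.** The smallest difference detectable with 80% power at 60 per group is 2.802 × 10.21 × √(2/60) = 5.22. Power therefore stays at 80% or more until saline yields 1 − 5.22/19.83 = 74% of the HES change. On the exchanged values there is no such margin.

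**4. What the fixed size detects with 80% power**, from 2.802 × SD × √(2/n):

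| Completers per group | SD 19.83 | SD 10.21 |
|---|---|---|
| 60 | 10.1 | 5.2 |
| 120 (only if the two doses are pooled) | 7.2 | 3.7 |

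**The case against.** The strongest reply is that the article never says the preliminary figure is a one-arm change. Mean difference is also the usual term for a contrast between groups, it stands directly above a two-group formula, and a condensed article need not describe a pilot's control arm. A reader might infer that the preliminary study was uncontrolled. The documents do not establish that, and a between-group reading is not strictly excluded. What remains is that the quantity is labelled "The mean difference and standard deviation of TTP after HES 130/0.4", that no saline figure appears anywhere, and that the between-group power is claimed all the same.

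A second reply is that nothing shows saline to move TTP, or by how much. The Background sentence on volume therapy is hedged as theory, and the article gives neither the repeatability of TTP nor its untreated course. That is correct. The 10% to 50% range is an assumption, and regression to the mean is a possibility of unknown size.

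A third reply is that on the printed numbers the loss of power disappears. That is also correct, but the printed numbers do not give 60 per group. The sponsor cannot rely on them for reassurance while keeping a sample size that only the exchanged numbers produce.

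**Conclusion.** The point holds in a limited form. The 80% between-group power in the Abstract and under Sample size estimates has no stated HES-minus-saline basis, so it is unsupported by the inputs shown.

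A reader might go further and infer that the trial is underpowered. The documents do not show that. Low power arises only if the values were exchanged and saline patients also change. Power at 60 per group then falls from 80% to between 71% and 29% for a saline share of 10% to 50%. If the printed order is right, 60 per group is ample unless saline yields about 74% or more of the HES change.

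The size of the exposure therefore turns on two facts that the article does not supply: which value is the SD, and what the saline response is. The claim should be restated, because it governs how a null result would be read.

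**What to change.** - Check against the preliminary data which of 19.83 and 10.21 is the mean difference and which the SD, give the units, and make the printed inputs agree with 60 per group.
- Define δ explicitly as HES minus NS. Do not describe the 80% power as following from the preliminary figure after HES.
- Replace the 80% claim with the difference detectable with 80% power at 60 completers per group: about 10.1 units if the SD is 19.83, about 5.2 if it is 10.21. Give the 120-versus-120 figures (about 7.2 or 3.7) only if the two doses are to be pooled, since the article states no pooled analysis and enrols the dose cohorts one after the other.
- Optionally, check the SD with the arms combined and blinded once the 500 ml cohort is complete, and update the detectable difference. This does not validate δ, because it says nothing about the saline response.

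The cost is rewording and, if wanted, one blinded calculation. No patients are added. The stated power becomes less favourable.

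### The stated mean difference (19.83) and SD (10.21) give about 5 per group in the printed formula, not 60; the two figures appear to be transposed

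*Protocol article*

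**What the plan says.** The section on sample size estimates in the protocol article takes its inputs from an unpublished preliminary study: "The mean difference and standard deviation of TTP after HES 130/0.4 were 19.83 and 10.21, respectively". It adds that "A two-sided 5% significance level and 80% power were considered" and prints the usual formula for comparing two means, n = 2(z for α/2 + z for β)²σ²/δ². Its result is "Approximately 60 participants in each group were calculated to be required". The last step is "A 20% attrition rate is anticipated over the 2-year study period, resulting in about 300 participants in total four groups". The four groups are the two fluids at two daily volumes (Study procedures), and the Study design section gives 1:1 allocation. The Abstract repeats the power claim: "The sample size will allow the detection of a two-sided 5% significance level between groups in the endpoint with a power of 80" (per cent). The article gives no other effect size or SD, and no unit for these two figures.

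**The concern.** The inputs, formula, error rates and result all stand in one short section, and they do not agree. A difference nearly twice the SD is a very large standardised effect, and a two-arm comparison of that size needs only a handful of patients per arm. A requirement of 60 per group points to an effect of about half an SD.

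This section is the only justification given for 300 patients and for 80% power. If the sentence is right, the trial is 12 to 14 times larger than its own calculation requires, and the 80% figure is wrong. If the sentence has the figures in the wrong order, the size stands, but the published planning difference is nearly double the one used and the published SD is about half. Anyone who judges the result against the planned effect, or reuses these figures to plan another trial, would be misled.

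**Working it through.** **Inputs, all from the protocol article.** Difference δ = 19.83 and SD σ = 10.21 as labelled; two-sided α = 0.05; power 80%; 20% attrition; four groups (Sample size estimates). Allocation 1:1 (Study design).

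**Multiplier.** (1.960 + 0.842)² = 7.849 with unrounded normal quantiles, so n per group = 2 × 7.849 × (σ/δ)².

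**Reproducing the article's figure with the inputs as labelled.**
2 × 7.849 × (10.21/19.83)² = 4.16, rounded up to 5 per group. The stated 60 is not reproduced.

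**Same formula with the two values exchanged (δ = 10.21, σ = 19.83).**
2 × 7.849 × (19.83/10.21)² = 59.2, rounded up to 60 per group. This matches.

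**Attrition and total.** 60/(1 − 0.20) = 75 per group, and 4 × 75 = 300. This step is correct as printed.

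**Can another convention reach 60 with the labelled inputs?**

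| Variant (δ = 19.83, σ = 10.21 unless noted) | n per group |
|---|---|
| One-sided 5% | 3.3, rounded up to 4 |
| 90% power | 6 |
| 95% power | 7 |
| 99% power | 10 |
| Multiplier 1 instead of 2 (one sample) | 2.1 |
| 10.21 read as a variance | 0.4 |
| SD × √2 | 8.3 |
| SD × 2 | 16.6 |
| α = 0.05/6 | 6.4 |

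None comes near 60. To reach 60 with SD 10.21, δ would have to be about 5.22. To reach it with δ = 19.83, the SD would have to be about 38.8. Neither value appears in the article.

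**What each reading implies at 60 per group.**

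| | As labelled | Exchanged |
|---|---|---|
| Standardised effect δ/σ | 19.83/10.21 = 1.94 | 10.21/19.83 = 0.515 |
| n per group for 80% power (formula) | 5 | 60 |
| Power, normal approximation | above 99.9% | 80.5% |
| Power, noncentral t | above 99.9% | 79.9% |
| Difference detectable with 80% power, σ√(2 × 7.849/60) | 5.2 units | 10.1 units |

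**Size of the discrepancy.** 60/5 = 12 with the rounded requirement, or 60/4.16 = 14.4 unrounded.

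**The case against.** The best defence is that this is a slip in one sentence. On the most plausible reading the figures were simply printed in the wrong order, and 60 per group, 80% power and 300 patients are all correct. On the other reading power is higher than claimed. Neither leaves the trial too small. That is right and limits the consequence: this is not a finding of low power. It does not remove the contradiction between the stated inputs and the stated result.

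A second objection is that two readings may not exhaust the possibilities. The sentence speaks of TTP after HES, which could mean a before-to-after change in treated patients, whereas the formula needs a difference between HES and saline. The δ actually used might then be a third, unprinted value. This cannot be excluded from the article, although the match at 59.2 makes exchange much the likelier explanation. The same check of the preliminary data would settle it.

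Third, the missing unit does not affect the arithmetic, because units cancel in σ/δ. That is so. The unit matters for interpretation only: eligibility is set as a percentage prolongation of TTP, so a reader cannot tell whether 19.83 and 10.21 are seconds or per cent, or judge which is the plausible difference.

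**Conclusion.** The point holds. With the inputs as printed, the article's own formula gives 5 per group, not 60, and 60 per group would have power above 99.9%, not 80%. Exchanging the two figures restores the 60, the 80% and the 300 together, so transposition is a strong inference. It remains unproven while the preliminary data are unpublished. The planning effect is 1.94 SD on one reading and 0.515 SD on the other, a 3.8-fold gap (1.94/0.515); in raw units it is 19.83 against 10.21. The calculation assumes that the printed formula was the one used and that δ is a between-arm difference in the primary outcome with a common SD. Because the sole stated basis for the trial's size contradicts its own result more than tenfold, it must be corrected.

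**What to change.** Go back to the preliminary data, establish which figure is the mean difference and which the SD, and confirm that the difference is between arms and not a change within the HES arm. Then:

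- **If the mean difference is 10.21 and the SD 19.83:** swap the two figures in the sentence and keep 60 per group, 80% power and 300 in total.
- **If the sentence is correct as printed:** withdraw the statements that 60 per group are required and that power is 80%, here and in the Abstract. State that 60 per group has power above 99.9% for a difference of 19.83, and 80% power for a difference of 5.2 units.
- **If neither figure is the between-arm difference that was used:** print the inputs that were used and show that they give the stated number.

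In every case give the unit of TTP (seconds or per cent). In the first two cases the cost is a change of wording, with no change in enrolment. In the third, enrolment can be judged only once the inputs are known.
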